## Abstract

**Background::**

Metabolic syndrome (MS) is a common chronic disease in modern society, and the etiology and pathogenesis of it is still unknown. For its main symptoms: disorder of glucose and lipid metabolism, the usual treatment is applying statin and hypoglycemic drugs. Comparing to the long-term application of these drugs which may cost great side effects, Dendrobium Nobile Lindl (DN) has been proved for its hypoglycemic and lipid-lowering effects without obvious side effects. So this trial is aim to evaluate the efficacy and safety of DN-powder in intervention of MS, and to explore the mechanism of action of DN through multi-group correlation analysis.

**Methods::**

This clinical trial is a single-arm, non-randomized, open, exploratory trial. A total of 30 participants who are suffering from MS will be assigned into therapy group (n = 30). The treatment course will last for 8 weeks, and a follow-up period for 4 weeks. The participants will receive DN-powder for 6 g, twice a day during the study period. The primary outcome will be the change of lipid and glucose metabolism. Other outcomes will be the body weight and body mass index (BMI) which will be assessments record in every 2 weeks. Participants who quit the trial due to untolerable reactions or uncontrollable conditions will enter into a follow-up period after the last treatment. All participants will enter into a follow-up period for 4 weeks after the last treatment. Adverse events will be recorded during the whole study.

**Discussion::**

The results of the trial are aim to provide evidence of the safety and efficacy of DN-powder in intervention of MS which may be potential to become an important alternative therapy for certain patients.

**Trial registration::**

It has been registered at http://www.chictr.org.cn/showprojen.aspx?proj=55914. (Identifier: ChiCTR2000034550), Registered 9 July 2020.

## Introduction

1

Metabolic syndrome (MS) is a common chronic disease which is characterized by obesity, dyslipidaemia, raised blood pressure and high glucose levels. It can shows hypertriglyceridemia (HTG) and/or low high-density lipoprotein cholesterol in the examination. And it is associated with the risk of type 2 diabetes and developing cardiovascular disease.^[1,2]^

Worldwide, the prevalence of MS usually corresponds to that of obesity and it is quiet different from age, gender, ethnicity and diagnostic criteria. The prevalence of MS was relatively high in Western countries. According to statistics, it was 38% in females and 41% in males in Europe.^[3]^ In the United States, 35% of adults and 50% of people over 60 which 35.6% in females and 30.3% in males were diagnosed as MS.^[4]^ Compared to the prevalence in the Middle East that females ranging from 32.1% to 42.7% while males ranging from 20.7% to 37.2%.^[5]^ In China, the prevalences were 19.2% in males and 27.0% in females while in the population over 60, the number rasied up to 58.1%.^[6,7]^

At present, the etiology and pathogenesis of MS are not completely clear. It is generally believed that central obesity is an initial factor and insulin resistance is the main pathogenesis of MS. Early diagnosis and intervention of MS can reduce the risk of diseases as atherosclerosis, stroke, cerebral hemorrhage even myocardial infarction.^[8,9]^ Regrettably, MS still lacks effective drugs today.

DN in Chinese Medicine is listed as the primary source of medicinal dendrobium in the *Chinese Pharmacopoeia* (2010)^[10]^ and has been used as a dietary additive for hundreds of years. In recent years, scholars have discovered that the chemical components of DN are mainly alkaloids, polysaccharides, flavonoids, phenols, sesquiterpenes, coumarins and steroidal glycoside compounds.^[11,12]^ Polysaccharides and alkaloids are the key to affecting lipid metabolism. Xu et al^[13]^ found that the dried stems of DN contained about 0.41% to 0.64% alkaloids, which was the highest concentration in various dendrobium plants.^[14]^ However the clinical study is still lacking, so we design this exploratory clinical trial to evaluate the safety and efficacy of DN-powder in intervention of MS.

## Methods

2

### Trial design and study setting

2.1

The trial is designed as a single-arm, non-randomized, open, exploratory clinical one. The protocol was written in accordance with Standard Protocol Items: Recommendations for Interventional Trials 2013 statement.^[15]^ The study protocol was approved by The Medical Ethics Committee of Longhua Hospital, Shanghai University of Traditional Chinese Medicine (No: 2020LCSY021), and informed consent will be obtained from each participant.

The trial will be conducted in Longhua Hospital, Shanghai University of Traditional Chinese Medicine, from July 2020 to June 2021 and 30 qualified participants will be recruited from public and will be allocated to the therapy group for 2 months. The flowchart is shown in Figure 1, and the timeline is given in Table 1.

**Figure 1 F1:**
[figure not shown]
Flowchart.

**Table 1 T1:** Timeline.

Study Period						
	Enrollment	Intervention				Close-out
Timepoint	0	Wk 2	Wk 4	Wk 6	Wk 8	Wk 12
Enrollment:						
Informed consent	X					
Inclusion or Exclusion criteria	X					
Baseline information	X					
Allocation	X					
Assessments:						
TG	X				X	
TC	X				X	
HDL-c	X				X	
LDL-c	X				X	
FFA	X				X	
FPG	X				X	
Body Weight	X	X	X	X	X	X
BMI	X	X	X	X	X	X
Safety assessments	X	X	X	X	X	X

BMI = Body mass index, FFA = free fatty acid, FPG = fasting plasma glucose, HDL-c = high-density lipoprotein cholesterol, LDL-c = low density lipoprotein cholesterol, TC = total cholesterol, Wk = week.

### Eligibility criteria

2.2

#### Inclusion criteria

2.2.1

Participants who meet all the following criteria will be recruited:

1.Aged between 18 to 65 years old, both genders;2.Meet the diagnostic criteria of MS:^[16–18]^① Overweight or Central obesity: BMI cut-off point for obesity (>24.0 kg/m^2^) or waist circumference ≥90 cm for males and ≥85 cm for females.② Hyperglycemia: fasting plasma glucose (FPG) ≥6.1 mmol/L (110 mg/dl) or 2 hour plasma glucose ≥7.8 mmol/L (140 mg/dl), or previously diagnosed type 2 diabetes.③ Hypertensive: systolic blood pressure ≥130 or diastolic blood pressure ≥ 85 mm Hg, or treatment of previously diagnosed hypertension.④ Raised TG level: fasting TG level≥1.7 mmol/L (150 mg/dl), or received treatment for this lipid abnormality.⑤ Reduced HDL-c: fasting blood HDL-c<0.9 mmol/L (35 mg/dl) for males and <1.0 mmol/L (39 mg/dl) for females.^∗^with 3 or all of the above 5 items can be diagnosed as metabolic syndrome.3.Agree to join this clinical study, volunteer to sign up informed consent form and agree to participate in all visits and inspections in accordance with the requirements of the study protocol.

#### Exclusion criteria

2.2.2

Participants who meet any of the following conditions will be excluded from the study:

1.Pregnant and lactating women;2.Combined with severe primary diseases, including but not limited to heart, liver, and kidney dysfunction, tumors and other serious cerebrovascular diseases.

### Intervention

2.3

#### Selection of DN

2.3.1

The origin of DN is from Guizhou, China. It is processed by Guizhou Natil Biotechnology Co., Ltd. as an agent. The company has the Certificate of Good Manufacturing Practices for Pharmaceutical Products, Drug Production License and Business License form People's Republic of China which will process DN-powder in accordance with the drug guidelines issued by the *Chinese Pharmacopoeia (2010)*.^[10]^ It is made to ensure that the DN-powder the company collects, processes and manufactures can be completely decomposed after being taken by the human body without leaving other chemical substance. Besides, Zunyi Medical University will conduct sampling composition determination, doing quality inspection and supervision of the decoction pieces to ensure that the DN-powder meets the specifications.

#### Instructions of DN

2.3.2

According to the standard oral administration method of DN published by the *Chinese Pharmacopoeia (2010)*.^[10]^ DN-powder was given a fixed dose of 12 g per day (twice a day, 6 g each time) to the subjects for oral on an empty stomach. 4 weeks is a course of treatment and the trail will take 2 courses in total. During the period, body weight and BMI will be record in every 2 weeks. After the treatment cycle, laboratory tests will be performed. Participants who quit the trial due to untolerable reactions or uncontrollable conditions will enter into a follow-up period after the last treatment. All participants will enter into a follow-up period for 4 weeks after the last treatment. Adverse events will be recorded during the whole study.

#### Intervention of diet and exercise

2.3.3

##### Diet intervention

2.3.3.1

Helping participants to establish a healthy diet refer to *Dietary Guidelines For Americans 2015–2020*^[19]^ which including focusing on diversity, nutritional density and quantity of foods; limiting the energy supply of sugars and saturated fatty acids; reducing sodium intake; switching to choose healthy foods and beverages. The total calories intake per day should be 2000 for female and 2400 for male.

##### Exercise prescription

2.3.3.2

The exercise prescription follows FITT principle which stands for frequency, intensity, time, and type of exercise. According to American College of Sports Medicine guidelines for exercise testing and prescription^[20]^ and requiring participants to do 150 minutes of moderate-intensity aerobic exercise (50%–70% of maximum heart rate; maximum heart rate = 220 - age) every week and record it.

#### Falling off criteria

2.3.4

For those who have to stop taking the drug due to serious adverse drug reactions; those whose treatment is ineffective and the participants give up to continue the trial; those who have poor compliance, or unwilling to obey the rules, or cannot complete the follow-up; and those who have no adverse reactions during the study, but for other reasons to interrupt the trial (such as immigration, lost follow-up, etc.).

#### Termination criteria

2.3.5

Participants withdrew their informed consent and asked to quit the trial; pregnancy incidents occurred during the study; side effects could not be tolerated; other situations that the researcher considered participants must quit the trial.

#### Combination medication statement

2.3.6

After joining the group, participants must maintain a standardized diet and a relatively stable amount of exercise. During the study period, no therapeutic drugs other than those specified in the study should be used; those with other diseases that must taking other drugs should be recorded in detail by the researcher.

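### Section 2.3.6 bars other drugs but section 2.2.1 admits treated patients: if entry lipid or glucose drugs are stopped, the single-arm change gains a component against DN-powder; if they continue, no dose rule applies.

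*Protocol article*

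**What the plan says.** Four parts of the protocol article bear on this.

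- **Section 2.3.6, Combination medication statement.** During the study period "no therapeutic drugs other than those specified in the study should be used". The same sentence then adds that "those with other diseases that must taking other drugs should be recorded in detail by the researcher". The article names no study drug other than DN-powder and does not say which diseases count as other.
- **Section 2.2.1, Inclusion criteria.** The triglyceride item can be met by a raised value "or received treatment for this lipid abnormality". The glucose item can be met by a raised value "or previously diagnosed type 2 diabetes". Treated hypertension likewise satisfies the blood-pressure item.
- **Section 2.2.2, Exclusion criteria.** Apart from pregnancy and lactation, the only exclusion is "Combined with severe primary diseases, including but not limited to heart, liver, and kidney dysfunction" and similar serious illness. No medication is an exclusion.
- **Table 1 and section 2.4.** The primary outcome is the change in TG, TC, HDL-c, LDL-c, FFA and FPG. Table 1 places consent, eligibility, "Baseline information" and the first laboratory tests at timepoint 0, and the only later laboratory tests at week 8. Section 2.4 collects past and concomitant medication at baseline. The article states no washout, run-in or stable-dose rule.

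**The concern.** One rule admits people who may be taking lipid- or glucose-lowering drugs, and another appears to forbid those drugs once they are in. These drugs act directly on the primary measures. With a single arm there is no control group in which a drug change would also occur and cancel out, so any change of background drug between timepoint 0 and week 8 enters the estimated effect.

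If a drug is stopped, week-8 lipids or glucose tend to rise (HDL-c tends to fall where the drug had raised it), and a real benefit of DN-powder can be masked. Stopping needed treatment would also matter for the participant, whatever it does to the analysis. If drugs may continue but the dose is free to move, an increase could pass for a benefit. This second risk is smaller, because the default ban already forbids new drugs.

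**Working it through.** The plan has no figure to reproduce here: section 2.5 sets n = 30 by expert consultation and gives no effect size, SD or power. The main check is therefore textual.

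**Which drugs does the ban reach?**

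1. The ban covers all therapeutic drugs not specified. The exception covers drugs needed for other diseases.
2. The abstract says of the syndrome's glucose and lipid disorder that "the usual treatment is applying statin and hypoglycemic drugs", and sets DN against them: "Comparing to the long-term application of these drugs which may cost great side effects". On that language, statins and hypoglycaemics treat the study disease, not another one, and so fall under the ban. This is the more natural reading.
3. Section 2.2.1 also names type 2 diabetes and hypertension as diagnoses in their own right. An investigator could treat these as other diseases and let the drugs continue. The text does not exclude this.

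**What follows for the primary outcome?**

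| Reading | Timepoint 0 | Week 8 | Effect on the change |
|---|---|---|---|
| Ban applies to entry drugs, stopped after the baseline sample | on drug | off drug | component against DN-powder |
| Ban applies, stopped before the baseline sample | off drug | off drug | component shrinks or vanishes |
| Exception applies, dose unchanged | on drug | on drug | none |
| Exception applies, dose changed | on drug | altered dose | either direction |

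The article does not fix which row applies.

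**Illustration of size. All inputs other than n = 30 and the .05 level are assumptions.** Use a paired t test on the change, two-sided .05, with within-person change SD set to 1. Section 2.6 names analysis of variance or a rank sum test; the paired t test is a simple stand-in.

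- Smallest significant observed mean change: t(.975, 29)/√30 = 2.045/5.477 = 0.373 SD.
- True benefit with 80% power (noncentral t): 0.529 SD.
- If k of 30 stop a drug worth s SD on that outcome, the mean moves by k·s/30. For k = 3 and s = 1 this is 3 × 1/30 = 0.10, leaving 0.529 − 0.10 = 0.429 SD. For k = 6 and s = 2 it is 0.40, leaving 0.129 SD.

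Probability of a significant benefit (simulation, 400,000 trials per cell; a repeat run agreed within 0.002):

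| k stopping | s = 0.5 | s = 1 | s = 2 |
|---|---|---|---|
| 0 | 0.80 | 0.80 | 0.80 |
| 1 | 0.772 | 0.735 | 0.641 |
| 3 | 0.711 | 0.589 | 0.292 |
| 6 | 0.608 | 0.355 | 0.035 |

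Here k is counted per outcome, since a lipid drug and a glucose drug need not move the same measures.

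For the looser reading, take no true effect and let k people start or increase a drug. The chance of a significant apparent benefit is 0.025 for k = 0. For s = 0.5, 1 and 2 it becomes 0.030, 0.034, 0.042 (k = 1); 0.043, 0.064, 0.110 (k = 3); and 0.070, 0.145, 0.343 (k = 6).

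**The case against.** A reader might infer that the protocol takes treated participants off their drugs after an on-drug baseline and so biases the result against DN-powder. The documents do not support that as a statement of fact, for these reasons:

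- **Stopping and its timing are not stated.** Nothing says that existing drugs are withdrawn, or when. The ban runs over the study period; Table 1 uses that term for the whole timeline including enrolment, while the abstract uses it for the dosing weeks. Table 1 gives visits, not the interval from last dose to sampling.
- **The exception may cover these drugs.** Section 2.4 expects concomitant medication, and the Discussion supports drug treatment of each component when preventive measures fail. That sits poorly with withdrawal.
- **Net direction is open.** Everyone also receives the diet and exercise programme (section 2.3.3), which pushes the uncontrolled change towards apparent benefit.
- **Few may be affected.** Section 2.2.1 refers to diagnosed, not drug-treated, diabetes, and neither route requires current drug use.
- **The full protocol may list permitted drugs.** The article condenses it. If background lipid and glucose drugs are on the specified list, the point reduces to aligning this wording and fixing the dose.

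All of this stands, and it limits the point to a conditional one. It does not remove it. Diet and exercise add a second bias of opposite sign and do not correct the first. The exception, read generously, still leaves the dose free. The investigator's power to withdraw or treat participants addresses adverse events once they occur; it does not say what to do with entry drugs.

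**Conclusion.** The eligibility criteria and the medication rule conflict as written, and the conflict touches the primary outcome. Applied to lipid- and glucose-lowering drugs taken at entry, the ban may produce an on-drug baseline and an off-drug week 8, which adds a component against DN-powder and a safety concern. If the exception applies instead, the drugs continue without a stable-dose rule. Neither reading protects the week-8 change.

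The article gives neither the share of treated participants nor an SD, so the size cannot be stated. The illustration shows only that a few people could matter with n = 30: from little loss (80% to 77%, one person, 0.5 SD) to almost none of the power left (about 3%, six people, 2 SD). It does not predict this trial's power, and the overall direction of bias is not determined. The point is worth an amendment now, because the change is small and recruitment is open (section 2.9). Confidence is medium, since the full protocol may settle part of it.

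**What to change.** Amend section 2.3.6 to say:

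- Lipid-, glucose- and blood-pressure-lowering drugs in use at entry continue at an unchanged dose through week 8 unless a change is clinically needed.
- No new drug of these classes is started unless clinically needed.
- Every start, stop or dose change is recorded at each visit.
- The exception for other diseases does not refer to the components of the syndrome, which the sentences above now cover.

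A breakdown of the primary changes by whether a relevant drug was changed can be shown, but as description only: it conditions on a post-baseline event in very few people. Leaving out 1, 3 or 6 people would give power of 79%, 75% or 70% at 0.529 SD instead of 80%.

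**Cost.** Participants already enrolled came in under the present section 2.3.6, so two rules would apply within 30 people, and the medication records of those enrolled must be checked for drugs stopped or changed. The data burden is small because medication is already collected at baseline. If the team wants DN-powder tested without these drugs, it could instead exclude current users among those not yet enrolled, at the price of slower recruitment. Neither change separates DN-powder from the diet and exercise programme.

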### Outcome measurements

2.4

Outcome will be performed by laboratory tests or physical examination after the intervention (at week 8).

Primary outcome will be the change of blood lipid and glucose which are the most intuitive assessments of the body. Main assessments of blood lipid includes TG, 3total cholesterol, HDL-c, low density lipoprotein cholesterol, free fatty acid and FPG.

Other outcomes are body weight and BMI. Weighing the body weight to see if there is any weight loss. Using the following formula to calculate BMI: Body weight in kilograms divided by height in meters squared. Recording body weight and calculating BMI at each visit, namely every 2 weeks. The evaluation will be performed in baseline and treatment endpoint. In addition, the researchers will keep in touch with participants via phone call, message or through the Internet to ensure the progress every day.

Baseline observation include demographic data (age, gender, occupation, education level), medical history, allergies history, past or combined medication, height, waist circumference. Assessments include clinical laboratory examination (TG, total cholesterol high-density lipoprotein cholesterol, low density lipoprotein cholesterol, free fatty acid and FPG), body weight, BMI, and safety assessments. Adverse events will be recorded throughout the study. Researchers will evaluate the severity of the adverse event and decide whether to continue the treatment or not. Participants with adverse events will receive necessary medical interventions. Participants who quit the study due to untolerable reactions or uncontrollable conditions will enter into the follow-up period after the last treatment. All participants will enter into the follow-up period for 4 weeks at the end of the treatment.

### Determination of sample size

2.5

The trial is a single-arm, non-randomized, open, exploratory clinical trial. For exploratory and safe considerations, it is designed as a small sample trial. The sample size cannot be calculated due to lack of database. For the determination of participants recruited in this trial, after consulting with experts in this field, we finally designed the sample size to 30 (n = 30).

### Statistical analysis

2.6

In the trail, Statistical Product and Service Solutions software will be applied to conduct statistical analysis. A full analysis set will be considered as the principal analysis and the per-protocol is set as the subset of full analysis set. The per-protocol will consist of participants who perform the study and have principal variable base-line values in this trial. The principal parameters will be conducted at baseline, each treatment and in the follow-up period.

Descriptive statistics will be used to balance baseline and parametric characteristics. Researchers will compare and analyze the data from baseline to the end of the follow-up period to confirm the difference between primary and other outcomes. When it comes to normal distribution, one-way analysis of variance will be used to compare subjective and semi-objective outcomes. Otherwise, it will be run by rank sum test. In the efficacy comparison stage, the outcome measurements before and after the intervention will adopt single factor analysis. For each outcome, *P* < .05 is considered statistically significant.

Multi-group correlation analysis include extraction and sample derivation of metabolites (blood samples and stool samples). GC-MS analysis Metabolomics instrumental analysis will be performed on an Agilent 7890A gas chromatography system coupled to an Agilent 5975C inert MSD system (Agilent Technologies Inc., CA). Principal component analysis is used to truly reflect the differences between groups, if the differences between groups are small, then the supervised model, namely Partial least squares-discriminant analysis will be used to eliminate interference. It will also adopt Student *t* test to identify differential metabolites and analyze correlation matrix.

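### The tests named for the before-after comparisons assume independent samples, although the trial has one arm and every efficacy comparison is within the same 30 people

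*Protocol article*

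**What the plan says.** Section 2.1 fixes the design: "The trial is designed as a single-arm, non-randomized, open, exploratory clinical one". Section 2.5 sets 30 participants on expert advice, because "The sample size cannot be calculated due to lack of database".

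Section 2.4 defines the main endpoint as a change: "Primary outcome will be the change of blood lipid and glucose". Table 1 schedules TG, TC, HDL-c, LDL-c, FFA and FPG at enrollment and week 8. Body weight and BMI are scheduled at six time points (0, 2, 4, 6, 8 and 12 weeks).

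Section 2.6 contains three relevant sentences. The scope is "Researchers will compare and analyze the data from baseline to the end of the follow-up period". The tests are then given: under normality, "one-way analysis of variance will be used to compare subjective and semi-objective outcomes. Otherwise, it will be run by rank sum test". For the efficacy comparison itself, "the outcome measurements before and after the intervention will adopt single factor analysis". Each outcome is judged at P < .05. The section mentions no paired t test, signed-rank test, repeated-measures ANOVA, Friedman test or mixed model.

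**The concern.** One-way ANOVA and the rank sum test are methods for independent samples. There is no second arm, so the only factor they could compare here is time, and the groups being compared are the same people counted again. The variation between people, which pairing would remove, then stays in the error term.

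The sentence that names the tests also misses its target. It applies ANOVA to subjective or semi-objective measures, while every listed efficacy outcome is a laboratory value, body weight or BMI.

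The fault reaches all efficacy outcomes, including the primary ones. In an exploratory study of 30 people without a control group, using each participant as their own control is the main source of precision. An analyst who follows the text would give it up and could report no difference where there is a change worth pursuing.

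**Working it through.** **What is being compared.** The protocol contains no power or sample-size calculation, so there is no stated figure to reproduce. The check compares the test named with the test that the design calls for.

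**Inputs from the protocol.** One arm (2.1), n = 30 (2.5), change from baseline to week 8 (2.4 and Table 1), alpha 0.05 per outcome (2.6).

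**Assumptions, not in the documents.** Two-sided testing, normal data, equal SD at both times, within-person correlation r between 0 and 0.9, and a true change expressed in SD of the outcome.

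**Standard error of the mean change**

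- Independent-sample: SD × √(2/n) = SD × √(2/30) = 0.258 SD, whatever r is.
- Paired: SD × √(2(1 − r)/n). At r = 0.5 this is SD × √(1/30) = 0.183 SD.
- Ratio: 1/√(1 − r).

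**Power for a change of 0.5 SD.** At r = 0.5 the paired test centres on 0.5/0.183 = 2.74, against a critical value of 2.05 on 29 degrees of freedom, which gives 75% power. The independent-sample test centres on 0.5/0.258 = 1.94, just below its critical value of 2.00 on 58 degrees of freedom. Its power therefore stays a little under one half at every r. Simulation with 200,000 trials per setting gives:

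| r | SE ratio | Power, independent | Power, paired | True type I error of the independent test |
|---|---|---|---|---|
| 0 | 1.00 | 48% | 46% | 5% |
| 0.3 | 1.20 | 47% | 61% | 2% |
| 0.5 | 1.41 | 47% | 75% | 0.7% |
| 0.7 | 1.83 | 47% | 93% | 0.07 to 0.08% |
| 0.9 | 3.16 | 45% | over 99% | about 0 |

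**Rank tests, same 0.5 SD change** (2,000 trials per setting). Rank sum against signed-rank: 47% against 61% at r = 0.3, 44% against 75% at 0.5, 44% against 92% at 0.7, and 45% against about 100% at 0.9.

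**Other effect sizes.** For a change of 0.3 SD, independent against paired power is 17% against 27% (r = 0.3), 13% against 36% (0.5), 8% against 54% (0.7) and 2% against 94% (0.9). For a change of 0.8 SD, the independent test still has 90%, 93%, 97% and over 99% power at the same correlations.

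**Change detectable with 80% power.** Paired: 0.63, 0.53, 0.41 and 0.24 SD at r = 0.3, 0.5, 0.7 and 0.9. The standard independent-sample formula gives 0.74 SD.

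**Weight and BMI over six visits.** Assume equal correlation between all visits and a linear total change of 0.3 SD. One-way ANOVA then has 2.4%, 0.3% and under 0.1% power at r = 0.5, 0.7 and 0.9. Repeated-measures ANOVA has 27%, 44% and 93%.

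**The case against.** **The before-after sentence does not say one-way ANOVA.** It says only that a single-factor analysis will be used, and a repeated-measures ANOVA with time as its one factor would also fit that term. Rank sum may likewise be loose wording for signed-rank. This objection stands in part. A reader might infer that the sponsor has definitely committed to unpaired tests, and the text does not go that far. However, the phrase comes soon after one-way ANOVA in the same paragraph, its plain reading is that test, and nothing signals pairing. If a paired analysis was meant, the wording still has to change.

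**Real changes will be missed.** A reader might infer this, but the documents cannot support it. The loss depends on a correlation and an effect size that they do not give. It is nil at r = 0, and a change of 0.8 SD or more would usually be detected either way.

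**A collapse in power.** Holding the paired test at 80% power takes the independent test to 53%, 25% and about 9% at r = 0.5, 0.7 and 0.8. Part of that fall arises because the raw change being tested shrinks as r rises (0.53, 0.41 and 0.33 SD). The fixed 0.5 SD comparison above avoids this.

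**False positives and confidence intervals.** The error does not inflate false positives; it lowers them. Nor can one say that planned confidence intervals are wrong, because the article plans none and gives only a P-value threshold.

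**Left to the analysis plan.** An article may leave detail to a later plan. Here the article names tests, and a later plan would have to contradict it to be right.

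**Conclusion.** Wrong as written. The tests named in section 2.6 do not fit a single-arm design in which every efficacy comparison is within person, and the condition attached to them matches no listed outcome. The consequence is conservative: with positive within-person correlation, standard errors and P values are too large and real changes may be missed.

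The size rests on assumptions. If the true change is 0.5 SD and r is 0.5 to 0.9, power is somewhat under one half instead of three quarters or more. The gap is wider for smaller changes and closes for large changes or weak correlation. The conclusion that the named methods are unsuitable needs none of these figures. It follows from the design and the plain meaning of the test names.

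**What to change.** In section 2.6, replace the sentence on ANOVA and the rank sum test and the sentence on single-factor analysis with text such as:

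*The change from baseline to week 8 in TG, TC, HDL-c, LDL-c, FFA, FPG, body weight and BMI will be analysed by the paired t test, or by the Wilcoxon signed-rank test if the differences are clearly non-normal. The mean change will be reported with its 95% CI.*

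If weight and BMI are to be compared across all visits, name a repeated-measures method for that. If only baseline and week 8 are compared, the paired test is enough. Delete the restriction to subjective and semi-objective outcomes.

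The cost is wording only: the data, visits and software stay the same. Make the change before analysis, because a switch of test after results are seen would look data-driven.
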